## Abstract

**Background:**

Currently, the number of children living with HIV is the highest ever. This has led to an increased focus on a healthy life expectancy in this population. Improving oral health status may contribute to improved immunity, which could in turn lead to greater overall health in this population. This study aims to evaluate the effectiveness of an oral health intervention in improving oral health and immune status among children living with HIV in Cambodia.

**Methods:**

A randomized controlled trial will be conducted in Phnom Penh from May 2018 to April 2020. Among 520 dyads of children living with their respective caregivers, half will be randomly allocated to the intervention group and the other half to the control group. Children aged 3–15 years who are currently receiving antiretroviral therapy at the National Pediatric Hospital will be recruited. In addition, 260 HIV-uninfected children (age-matched to the intervention group) will be recruited from the communities. They, together with their caregivers, will comprise the second control group. The main components of the intervention will include oral health education sessions for the children, as well as daily oral self-care under the supervision of their caregivers. The primary study outcome will be the change in oral health status including the number of decayed, missing, or filled permanent teeth, and the secondary outcome will be CD4 count. The effects of the intervention will be assessed by comparing outcome indicators between the children in the intervention and those in the control groups.

**Discussion:**

This trial will investigate the effects of an oral health intervention on the improvement of oral health and immune status among children living with HIV and determine the differences compared with the control groups. This intervention would encourage the promotion of oral health interventions among children living with HIV and thus contribute to delaying the onset of AIDS.

**Trial registration:**

Current Controlled Trials, International Standard Randomized Controlled Trial Number Register, ISRCTN15177479. Registered on 17 January 2018.

**Electronic supplementary material:**

The online version of this article (10.1186/s13063-018-3047-z) contains supplementary material, which is available to authorized users.

## Background

Antiretroviral therapy (ART) has reduced the incidence of new HIV infections worldwide by two thirds in the last 15 years [1]. Accordingly, the lives of many people living with HIV have been saved, and their life expectancies have increased. In high-income countries, the life expectancy of people living with HIV who begin ART at 20 years of age has increased from 36 to 49 years, similar to that of the general population [2]. Among children living with HIV, the mean life expectancy has doubled from 9 to 18 years [3], and the majority of children living with HIV receiving ART in low- and middle-income countries have reached adolescence [4]. These therapeutic advances have yielded the highest-ever number of people living with HIV worldwide, approximately 36.7 million in 2016 [1]. This expansion has led to an increased focus on a healthy life expectancy in this population, although further improvement is required.

Oral health has been identified as a key factor in a healthy life expectancy [5]. In general, a healthy oral status correlates with various parameters of overall health, such as immunity, nutrition status, and cognitive function [6–9]. In addition to dental problems, an unhealthy oral status may affect the healthy physical and mental development of children due to malnutrition, developmental delays, or a lower quality of life [10, 11]. An unhealthy oral status may also predispose one to future lifestyle diseases [12] and may correlate with a high number of disability-adjusted life years [13]. Therefore, the World Health Organization (WHO) recommends initiating oral health care during early childhood [9, 14].

Previous studies have also considered the relationship between oral health and overall health status among adults living with HIV. Periodontal disease was found to correlate with the development of AIDS [15, 16]. A lower immune status has been suggested to correlate with the frequency of oral lesions [17] or caries [18, 19]. HIV-infected people with an advanced stage of immune suppression are often diagnosed with xerostomia due to the reduction of salivary flow. Lower salivary flow hinders the salivary pH level recovery, thus making the oral environment favorable to dental caries [20, 21]. However, studies evaluating the effectiveness of an oral health intervention in improving the overall health status remain scarce among people living with HIV, and a higher level of evidence, such as that generated through a randomized controlled trial, is needed. Particularly, it would be extremely important to determine a causal relationship between oral health and the immunity level, which is generally measured by CD4 count, to contribute to a delayed onset of AIDS. It is particularly important to address these issues in children living with HIV, given the potential effects of poor oral health and malnutrition on maturation to adulthood and the finding that the transition from infection to AIDS and death is compressed in children [22]. Early evaluation and treatment of oral health would therefore be particularly important in terms of the quality of life and longevity in the pediatric population [22].

Furthermore, studies should investigate similarities and differences in the oral health status of children living with HIV relative to that of their HIV-uninfected peers, particularly in response to an oral health intervention. Oral health may have a more prominent effect on overall health status among children living with HIV; this population tends to develop more dental caries [22] and have worse oral lesion statuses [23, 24] relative to their uninfected peers. These discrepancies are partly attributable to the use of ART [22].

Although Cambodia has successfully reduced the incidence of new HIV infections, the prevalence of HIV in the general population remains high (0.6% in 2014) relative to that of other Asian countries [25]. In Cambodia, an estimated 4200 children aged younger than 15 years are currently living with HIV [26]; 87% of these children received ART in 2016 [27]. Concomitantly, pediatric oral health is a critical issue in Cambodia. According to the WHO, the estimated mean number of decayed, missing, or filled teeth (DMFT) among 12-year-olds in Cambodia was 5.50 between 2010 and 2012, compared to the global and Western Pacific Region averages of 1.67 and 1.39, respectively [28]. A study of 6-year-old children conducted in Pailin, Kampong Thom, and Kratie, Cambodia, reported the estimated mean number of DMFT as 7.90 [29]. In another study of school children conducted in the capital city of Phnom Penh, the reported mean DMFT was 2.33 [30]. Further, a study conducted in Siem Reap found that more than half of all children aged 6–16 years had dental caries in their permanent teeth [31], a condition that has been largely attributed to poor tooth brushing habits [31, 32]. Oral health is therefore an emerging public health issue in Cambodia that must be addressed.

The proposed research aims to adopt continual and affordable approaches, such as daily oral care, with an intention to improve the overall health status of children living with HIV in Cambodia. The specific objectives of the study are as follows:To examine the effectiveness of the daily oral care intervention in improving the oral health status of these children, particularly suppressing the increment in the number of DMFT relative to their HIV-infected and HIV-uninfected peers without interventionTo examine the effectiveness of the daily oral care intervention on overall health status, particularly including immunity level, nutrition status, and quality of life, relative to their HIV-infected and HIV-uninfected peers without intervention.

## Methods/design

### Study design and sites

This randomized controlled trial will be conducted from May 2018 to April 2020 within the catchment area of the National Pediatric Hospital in the capital city of Phnom Penh. The hospital comprises all diagnostic and treatment departments, including pediatric HIV and dental clinics. This hospital serves as a referral hub for health centers that provide routine pediatric care and treatment, and it is the only health facility to provide pediatric ART in Phnom Penh. See Additional file 1 for the Standard Protocol Items: Recommendations for Interventional Trials (SPIRIT) checklist.

### Study population and selection criteria

The study will comprise three groups: an intervention arm (group A) and two control arms (groups B and C) (see Fig. 1). The targets of groups A and B will be children living with HIV and their caregivers. Randomization will be performed for groups A and B using a 1:1 allocation protocol. The targets of group C will be HIV-uninfected children and their caregivers, comprising children age-matched with those in group A. Children eligible for groups A and B of the trial must meet all of the following inclusion criteria at randomization: (1) age 3–15 years, (2) have a patient ID at the National Pediatric Hospital, and (3) have received ART for at least 3 months. Children eligible for group C must be aged 3–15 years and must not have been diagnosed with HIV infection. For caregivers in all groups, individuals will be eligible if they are aged ≥ 18 years and self-report as the primary caregiver of the respective child.

**Fig. 1 Fig1:**
[figure not shown]
Flow diagram of subject selection

### Interventions

Children and caregivers in group A will receive an intervention for 2 years (May 2018–April 2020). The main components of the intervention will comprise oral health education sessions and daily oral self-care. Prior to the intervention, two dental assistants from the National Pediatric Hospital will be appointed to receive a 1-day training course in conducting the oral health education sessions and intervention follow-up. Subsequently, these professionals will disseminate oral health education sessions to the children and caregivers under the supervision of the dentist every 4 months during the 2-year intervention period (in total six sessions for each participant). The initial education session will be provided with the contents presented in Table 1. The dental assistants will also provide the follow-up sessions to the initial session. Each 60-min session, including practice of the oral health procedure, will be attended by groups of 10 child-caregiver pairs. The education session will aim to teach the children and caregivers about correct brushing and the importance of daily oral care. Teaching tools will be developed based on publicly accessible basic oral health education materials which are used in Japan and the USA at school or dental clinics [33, 34].

**Table 1 Tab1:** Contents of oral health education session

Session 1: Knowledge	
1. What is tooth decay?	
2. Causes and prevention of tooth decay	
Session 2: Practice	
1. Brushing	
2. Flossing	
Session 3: Evaluation of oral health status	
1. Check plaque status using tester	
Session 4: Home-based daily oral care	
1. What one needs to do at home for daily care	
2. Follow-up schedule	

The children and caregivers will practice home-based daily oral care. Each child will receive a toothbrush, two tubes of fluoride-containing toothpaste, and three packs of dental floss at every education session. During the session, the children will be advised to brush daily after breakfast, lunch, and dinner by themselves or with the help of a caregiver at home. To maximize the intervention adherence, the children will receive a daily record notebook to keep their daily oral care practice. In the notebook, a short oral care guide is presented to which the children and caregivers can refer any time at home. Also, the children affix a seal to the daily record notebook after each brushing and evaluate their weekly oral health practice on the checklist. The intervention will be discontinued at any time should the participant request it. Participants can receive any concomitant care and intervention during the trial.

The participants of groups B and C (randomized control arms) will not receive specific interventions for oral health management. Participants in all groups can receive any type of dental care as needed at a clinic, but they will be responsible for any expenditure.

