### Sample size

We calculated the sample size for the intervention and control groups as follows. We estimated that the intervention may suppress the increment of DMFT for around 17% based on the results of a previous study conducted in Cambodia among 8000 uninfected school children in five provinces. In that study, increments of DMFT of intervention and control groups were 0.82 and 0.99, respectively, after a 2-year intervention [35]. According to our situation analysis survey, which was conducted at the same study site in February 2017, for children living with HIV aged 8–15, the mean DMFT was 4.34 (standard deviation 3.3). We estimate that the intervention may suppress the increment of DMFT by 0.7 point, which equates to the 17% decrease in the mean DMFT. To detect this difference in our intervention group, at a power of 80% and a 5% significance level, 260 samples will be required for each group with a potential attrition of approximately 10%. In total, 780 pairs will be required for the three groups.

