### Statistical analyses

Baseline and endline surveys will be conducted to assess changes in each outcome in both the intervention and control groups. To minimize overestimation of intervention impact, all intervention outcomes will be estimated with an intention-to-treat analysis. Initially, survey data will be stratified by different age groups: 3–5 years old, 6–11 years old, and 12–15 years old. Then, the data will be descriptively analyzed to assess the distributions of various factors related to the children and caregivers under the study. Next, bivariate analyses will be conducted to assess the correlations of each oral health indicator (DMFT, debris index, bacterial number, salivary pH, salivary flow, oral-health related quality of life) with different variables, using the chi-square test (or Fisher’s exact test when a count is smaller than five) for categorical variables, and Student’s *t* test for continuous variables. Then, we will apply a generalized estimating equation model [41] adjusted for basic demographic characteristics (e.g., sex) and factors identified as significantly associated with the outcome in the bivariate analyses. The statistical significance will be set at a *p* value < 0.05. All data analyses will be performed using IBM SPSS, version 24.0 (SPSS Inc., Chicago, IL, USA).

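### Teaching arm A in groups of 10 pairs may create clustering in that arm only; the sample size makes no allowance for it and the planned GEE names no cluster unit.

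*Protocol article*

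**What the plan says.** All places are in the protocol article.

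- **Allocation** (Study population and selection criteria): "Randomization will be performed for groups A and B using a 1:1 allocation protocol". The unit randomized is the child with the caregiver, not a group.
- **Delivery in arm A** (Interventions): "Each 60-min session, including practice of the oral health procedure, will be attended by groups of 10 child-caregiver pairs". Sessions recur every four months for two years, "in total six sessions for each participant". For delivery, "two dental assistants from the National Pediatric Hospital will be appointed to receive a 1-day training course". The section does not say whether the same ten pairs meet each time.
- **Home component in arm A** (Interventions): "The children and caregivers will practice home-based daily oral care". This part is carried out family by family.
- **Controls** (Interventions): groups B and C "will not receive specific interventions for oral health management", so they have no session groups.
- **Sample size**: for a 0.7-point difference, SD 3.3, 80% power and 5% significance, "260 samples will be required for each group with a potential attrition of approximately 10"%. No ICC or design effect appears.
- **Statistical analyses**: "we will apply a generalized estimating equation model", adjusted for demographic factors and for variables significant in bivariate screening. The cluster unit, working correlation and type of standard error are not given. The only repeated structure described is the pair of baseline and endline surveys.

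**The concern.** Individual randomization with group delivery in one arm is a partially nested design. Children who attend the same sessions share the occasion, the practice and their peers, so their results may resemble one another more than those of two arbitrary children in the arm. Arm B has nothing comparable.

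If that correlation is positive and the GEE clusters only on the child, the standard error for A versus B is too small. A nominal 5% test then rejects too often, and the intervals are too narrow. If the analysis does account for the groups, the test keeps roughly its level but the trial has less power than a calculation for independent children implies. A given analysis suffers mainly one of these harms, not both in full.

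There is also a practical point. An analysis plan written later can cluster on education group only if membership was recorded during delivery. The Follow-up section lists what the research assistants note after each session, and a group identifier is not in that list. The article may simply have condensed it, but the item is worth securing.

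**Working it through.** **The plan's own figure.** Two means, two-sided 5%, 80% power:

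n = 2 × (1.960 + 0.842)² × 3.3² / 0.7² = 348.9, so 349 evaluable per arm, and 349 / 0.9 = 388 with 10% attrition.

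The stated 260 (about 234 evaluable) is not reproduced. One-sided, the figures are 275 and 306. Why 260 does not follow from its inputs is a separate matter. What counts here is that the stated number hides no reserve that could be read as an allowance for clustering.

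**Inputs for clustering.** Group size m = 10 (Interventions). Number of groups in A = 260 / 10 = 26. Arm B: independent children. ICC: not in the documents, so assumed at 0.01, 0.02, 0.05 and 0.10. Membership: assumed stable over the six sessions.

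**Formulas.** With n children per arm and common variance s²:

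- Var(A − B) = (s²/n) × [1 + (m − 1) × ICC] + s²/n
- Ratio R to the independent case = 1 + (m − 1) × ICC / 2 = 1 + 4.5 × ICC
- True standard error / child-level standard error = √R
- Type I error of a child-level analysis = 2 × [1 − Φ(1.96/√R)]
- Power of an analysis that accounts for the groups, from a nominal 80% = Φ(2.802/√R − 1.96)
- Evaluable children per arm to keep 80% = 234 × R, rounded up, then divided by 0.9

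| Assumed ICC | R | SE ratio √R | Type I error, child-level analysis | Power, group-aware analysis | 260 per arm becomes |
|---|---|---|---|---|---|
| 0 | 1.000 | 1.00 | 5.00% | 80% | 260 |
| 0.01 | 1.045 | 1.02 | 5.52% | 78% | 273 |
| 0.02 | 1.090 | 1.04 | 6.05% | 77% | 285 |
| 0.05 | 1.225 | 1.11 | 7.66% | 72% | 319 |
| 0.10 | 1.450 | 1.20 | 10.36% | 64% | 378 |

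The type I and power columns describe two different analyses. Under the child-level analysis, a nominal 80% power would fall only to Φ(0.842/√R) = 79.5%, 79.0%, 77.6% and 75.8%. The last column takes 260 as correct for ICC 0; it shows scale and is not a proposed enrolment.

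**After attrition.** With 9 evaluable children per group, √R is 1.020, 1.039, 1.095 and 1.183, so the picture hardly changes. A simulation of 26 groups of 9 against 234 independent children (20,000 runs) gave a child-level type I error of 7.5% at ICC 0.05 and 10.2% at ICC 0.10. Using the variance between group means in arm A gave 5.3% and 5.6%.

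**Starting from the power the stated inputs give.** With 234 evaluable per arm, a 0.7-point difference and SD 3.3, two-sided power is 63.1% before any clustering. Accounting for the groups gives 61.2%, 59.4%, 54.5% and 47.8% at the four ICCs.

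**The case against.** The strongest reply is that the article never says children are treated as independent. It names a GEE and stops there. A GEE can cluster on education group, and the choice of subject variable and correlation structure is often left to an analysis plan, which is not shown. This stands. A reader might infer that the planned analysis is wrong and that its intervals will be too narrow. The documents do not support that: they leave the cluster unit open, and the harm arises only if the unit is the child and the ICC is positive.

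Second, the cluster itself is uncertain. A group size is stated, but not fixed membership over six sessions. Changing membership would tend to weaken the correlation and blur what the cluster is. Contact is six hours in two years (6 × 60 minutes), and much of the intervention happens at home. This also stands, and it argues for the lower part of the ICC range. For CD4 count, the documents give no particular reason to expect correlation among children who share a session.

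Third, two dental assistants deliver all sessions, so any effect of the teacher spans many groups, and clustering on groups of 10 would not capture it. This is correct and limits what the fix can do.

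The objection does not reach two points. The protocol itself fixes the sample size, with no allowance for a feature of delivery that the same protocol describes. And a later analysis plan cannot use a group identifier that nobody recorded.

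**Conclusion.** The point holds as an inexpensive improvement, not as a demonstrated error. The design allows clustering in arm A only, the sample size ignores it, and the GEE is not tied to a cluster unit that would handle it.

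The size depends on an ICC that the documents do not give. At 0.01 to 0.02 the child-level standard error would be short by a factor of only 1.02 to 1.04, which is minor. At 0.05 to 0.10 the factor is 1.11 to 1.20, and a nominal 5% test would run at about 7.7% to 10.4%. These figures assume stable groups of 10, equal variances and no further correlation through the dental assistants. At the low end of the range, this matters less than the separate failure of 260 per arm to follow from its stated inputs.

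**What to change.** 1. Record the education-group identifier for each pair at every session, and keep pairs in the same group where this is feasible.
2. In Statistical analyses, name the GEE cluster for A versus B: the education group in arm A (the initial group if membership changes) and the single child in arm B. Keep both time points of a child inside the cluster and use robust standard errors.
3. In Sample size, state the assumed ICC range and the power that results.
4. Acknowledge that this does not capture an effect of the two dental assistants. With only two of them, it cannot be estimated reliably.

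**Cost.** One form field, a sentence or two in each section, and no extra enrolment. The price is in precision as reported: confidence intervals about 2% to 20% wider over ICC 0.01 to 0.10, and a stated power that becomes less favourable (78% down to 64% from a nominal 80%). Restoring 80% would need more children, as the last column of the table shows; that is not part of this proposal.

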### Recruitment

Recruitment will be conducted via a multiple-step process. First, children living with HIV aged 3–15 years will be identified from the patient lists of the National Pediatric Hospital. According to the list, 1113 children are eligible based on the study criteria. Twenty children in each age category from 3 to 15 years old will be randomly selected from each list to yield 260 children each for groups A and B. Second, the same patient lists will be used to identify one district wherein the largest number of children living with HIV reside. The children in group C will be selected from that district, using lists of residents aged 3–15 years that have been compiled by a local non-governmental organization, in collaboration with the local authorities. Twenty children per age category from 3 to 15 years will be randomly selected from those lists to yield 260 children for group C. The children deemed eligible for the intervention will be provided with information about the study, and the research assistants will seek an expression of interest from the caregivers and the children. They will be contacted by the research assistants to arrange a suitable time for the baseline survey. Prior to the survey, the research assistants will obtain their written informed consent.

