### Randomization

After the baseline survey, the children living with HIV will be randomly allocated to an intervention group in a 1:1 ratio. A computerized algorithm will be used to generate a randomization scheme to assign participants to the study arms. The allocation will be implemented by a data analyst who is not a primary member of the study team. A member of the research team will inform the participants of their allocation. The research assistants, principal investigator, and primary study team members will be blinded to the group allocations until after the participants have completed the baseline assessment.

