## Discussion

Here, we have described a study protocol for a randomized controlled trial to evaluate the effectiveness of an oral health intervention program in improving oral health status, which in turn will improve the immunity and overall health status of children living with HIV in Phnom Penh, Cambodia. This trial aims to investigate how the improvement of oral health status can contribute to the improvement of overall health status in a cohort of children living with HIV, compared with their HIV-infected and HIV-uninfected counterparts who do not undergo the oral health intervention. If proven effective, this oral health intervention could be suggested as another means to delay the onset of AIDS in this population and would lead to the further encouragement of oral health interventions for children living with HIV.

However, the proposed study has some limitations. First, the intervention will target children living with HIV receiving ART. Therefore, we will not be able to distinguish between the effects of ART and that of the oral health intervention on CD4 count or oral health status. Second, samples will be recruited only at one national hospital, and therefore this is a potential source of sampling bias. However, this study has the potential to provide strong evidence regarding the effectiveness of an oral health intervention in an area concentrated with children with HIV receiving ART.

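### Group C is called a randomised control arm and used to judge effectiveness, but it is a non-randomised HIV-uninfected sample; only A versus B can show what the intervention does.

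*Protocol article*

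**What the plan says.** The Interventions section of the protocol article puts both control groups under one label: "The participants of groups B and C (randomized control arms) will not receive specific interventions".

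Other sections describe the design differently:

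- Study population and selection criteria: "Randomization will be performed for groups A and B using a 1:1 allocation protocol". For the third group it says: "The targets of group C will be HIV-uninfected children and their caregivers, comprising children age-matched with those in group A". The eligibility rule is: "Children eligible for group C must be aged 3–15 years and must not have been diagnosed with HIV infection".
- Randomization: "After the baseline survey, the children living with HIV will be randomly allocated to an intervention group in a 1:1 ratio". Group C has no part in this step.
- Recruitment: A and B come from the hospital's patient lists. For C, the district where most of the listed children live is identified first, and then: "The children in group C will be selected from that district". Twenty children per year of age are drawn at random from that district's resident lists. This is random sampling, not random allocation.

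Group C is nevertheless used to judge the intervention. The first objective, at the end of the Background, concerns effectiveness in suppressing the increment "in the number of DMFT relative to their HIV-infected and HIV-uninfected peers" who receive no intervention. The second objective uses the same two comparators for overall health. The Data collection section assesses intervention effects by comparing group A with both control groups at baseline and endline.

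The limitations in the Discussion do not say that C is not randomised. They do say, of a trial in which all HIV-positive participants take ART, that "we will not be able to distinguish between the effects of ART and that of the oral health intervention on CD4 count" or on oral health status.

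**The concern.** A comparison supports a claim of effectiveness when the groups differ, apart from chance, only in the intervention. A versus B meets that condition. A versus C does not: group A has HIV, takes ART, comes from a hospital list and receives the intervention, while group C has no HIV diagnosis, comes from a district resident list and receives nothing. The Background itself says that children with HIV tend to have more caries and worse oral lesions than uninfected peers, and that ART explains part of this. The protocol thus names two causes of the outcome that coincide with group membership in A versus C.

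If A versus C is read as an effectiveness result, an intervention that works could appear useless or harmful, and one that does nothing could appear to work. Calling C randomised invites that reading. The ART limitation, read literally, has the opposite fault: it casts doubt on the one comparison in which ART is not a confounder.

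**Working it through.** **1. Who has what.** From the selection criteria, Interventions and Recruitment sections:

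| | A | B | C |
|---|---|---|---|
| HIV | yes | yes | no diagnosis |
| ART for at least 3 months | yes | yes | not applicable |
| Sampling frame | hospital list | hospital list | one district's resident list |
| Intervention | yes | no | no |
| Randomly allocated | yes | yes | no |
| Age range 3–15, 20 per year of age | yes | yes | yes |

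A and B differ in one row, the intervention. A and C differ in every row except the last.

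**2. What each contrast estimates.** Let e be the reduction in the 2-year DMFT increment that the intervention produces in children with HIV. Let h be the amount by which the untreated increment in HIV-positive children on ART from the hospital list exceeds that in group C. In expectation:

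- A − B = −e
- B − C = h
- A − C = (A − B) + (B − C) = h − e

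A versus C is the sum of the other two contrasts and adds nothing about e that A versus B does not give. Taking e = 0.7, the plan's target effect, as an example:

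- h = 0.7 gives A − C = 0, so no visible benefit.
- h = 1.0 gives +0.3, apparent harm.
- h = −0.3 gives −1.0, an exaggerated benefit.

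**3. Can adjustment help?** The Statistical analyses section plans a generalized estimating equation model adjusted for demographics and for factors found significant in bivariate analyses. Within A and C alone, HIV status and ART are each identical to the group indicator, so no model can separate them from the intervention. If B is added with a term for HIV status, the intervention coefficient becomes the A versus B contrast. A difference in response between infected and uninfected children, which the Background raises, would need treated uninfected children, and there are none.

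**4. How large could the error be?** The documents do not give h, so only an assumed range is possible. Inputs from the Sample size section are 260 per group, about 10% attrition and SD 3.3. That SD belongs to the DMFT level; using it for the change is an assumption.

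- Completers: 260 × 0.90 = 234 per group.
- Standard error: 3.3 × √(2/234) = 0.305.
- With no intervention effect (e = 0) and background shift h, P(two-sided p < 0.05) = Φ(h/0.305 − 1.96) + Φ(−h/0.305 − 1.96).

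| Shift h (DMFT) | Chance of p < 0.05 with no intervention effect |
|---|---|
| 0 | 5% |
| 0.3 | 17% |
| 0.5 | 37% |
| 0.7 | 63% |
| 1.0 | 91% |

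The table is the same for negative shifts. The 260 serves here only as the planned group size. The usual two-sided formula with 0.7, SD 3.3 and 80% power gives 349 per group, or 388 after 10% attrition, so 260 is not reproduced. That is a separate matter and does not bear on this point.

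**5. CD4.** The Data collection section takes CD4 only in A and B, so no A versus C comparison of CD4 exists, although the second objective names immunity against uninfected peers. In A versus B all children are on ART and allocation is random, so ART is not confounded with the intervention.

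**The case against.** The best defence is that the label is a single slip. The Abstract, selection criteria, Recruitment and Randomization sections all describe the structure correctly, and a careful reader would not take C as randomised. The Background gives a descriptive reason for an uninfected group, which is legitimate. Age is balanced. The analysis section specifies no A versus C model, and the choice of inferential contrasts is often left to an analysis plan. All of this stands, but it does not answer the objectives and the Data collection section, which use C to judge effectiveness in so many words.

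A reader might infer more than the documents support on four points.

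- **Size and direction of bias.** The Sample size section gives mean DMFT 4.34 in HIV-positive children aged 8–15 at the site, and the Background gives 2.33 in Phnom Penh school children, so one might put the bias at 4.34 − 2.33 = 2.01, nearly three times the 0.7 target. But these are DMFT levels, possibly at different ages, and the outcome is change. The Background also gives 5.50 for Cambodian 12-year-olds (4.34 − 5.50 = −1.16) and 7.90 for 6-year-olds in three areas (4.34 − 7.90 = −3.56), which reverse the sign. Neither size nor direction is established.
- **Residence.** It differs only in part. C comes from the district where most of the listed HIV-positive children live, and some of group A may live there.
- **The ART limitation.** It can be read as a remark on scope, since no child with HIV off ART is studied, and the same section still expects strong evidence of effectiveness. It is badly worded rather than a surrender of the causal claim. Confining it to comparisons with C would not work for CD4, which C does not have.
- **P-values.** Nothing requires banning a test of A versus C. What must go is the effectiveness claim.

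**Conclusion.** The point holds. The label on group C contradicts the protocol's own account of randomisation, and the objectives use a contrast that cannot estimate effectiveness. This follows from the design and rests on no numerical assumption: HIV status and ART coincide with group in A versus C, and no uninfected group is treated.

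The size and sign of the bias in the DMFT increment are unknown. The 17% to 91% range for false-positive results holds only under 234 completers per group, SD 3.3 for the change, no intervention effect, and a background shift between 0.3 and 1.0 DMFT. It shows sensitivity and is not an estimate.

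It would be wrong to conclude that the trial as a whole is confounded. A versus B is randomised and unaffected, for CD4 as well as DMFT. The problem lies in the wording of the objectives, one label, the comparisons with C, and the limitations.

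**What to change.** 1. In Interventions, call group B the randomised control arm and group C a non-randomised, HIV-uninfected reference group.
2. In the objectives, Data collection and Statistical analyses sections, state that effectiveness on all outcomes is judged on A versus B only.
3. Report comparisons with C as descriptive and without an effectiveness claim: B versus C for the HIV-associated difference without intervention (HIV and ART together), and A versus C for the gap that remains with it.
4. Add to the limitations that group C was not randomised and comes from a different sampling frame.
5. Reword the ART limitation. In A versus B all children are on ART, so the intervention effect, including that on CD4, is not confounded with ART. The limitation is that the results apply only to children receiving ART.

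The cost is protocol and analysis wording; no recruitment, measurement or sample size changes. The downside is that one claimed effectiveness comparison is given up.
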